# Promoting neuroplasticity and neuropsychological functioning in frailty through an app-based sensorimotor training: study protocol for a randomized trial

**DOI:** 10.1186/s12877-021-02293-9

**Published:** 2021-06-03

**Keywords:** Frailty, Neuroplasticity, Training app, Sensorimotor functioning, Aging

## Abstract

**Background:**

Frailty is characterized by an age-related decline in multiple physiological systems, leading to a high vulnerability to stressors, adverse health outcomes, and low quality of life. Neuroscientific models of pathological aging emphasize the loss of sensorimotor stimulation and reduced neuromodulatory capacities as core processes in age-related cognitive and bodily decline, which may be associated with maladaptive plastic changes in the brain. We plan to increase sensorimotor stimulation in frail persons through a newly developed app-based training program and link the training trials to biological and psychological correlates of age-associated vulnerability and health indices.

**Methods:**

We will conduct a randomized trial, applying an app-based sensorimotor home training (N = 30) in people suffering from frailty. An app-based relaxation training will serve as an active control condition (N = 30). Both interventions will last for 90 days each. The sensorimotor training includes unimodal and multimodal sensory discrimination tasks in the visual, auditory, and tactile domain, as well as sensorimotor precision tasks. The tasks will be implemented using an adaptive training algorithm and enriched with motivational components embedded in a virtual training environment. We expect a pre-post reduction of frailty status and associated functional decline related to refinement of representational maps within the sensorimotor system and improved sensorimotor function such as extremity function. Secondary analyses will study the influence of BDNF genotype as moderating variable. Additional outcomes will include measures of perceptual and cognitive functioning, quality of life as well as BDNF serum levels. Measurements will take place before training (baseline), after 60 days (assessment 1), and at the end of the training after 90 days (assessment 2).

**Discussion:**

In our randomized trial, we aim to characterize a multidimensional concept of frailty and to target maladaptive behaviors and neuroplasticity using an app-based sensorimotor training. This type of intervention might provide further knowledge and new possibilities for preventing decline and preserving function in older adults.

**Trial registration:**

ClinicalTrials.gov NCT03666039. Registered 11 September 2018 – Retrospectively registered.

Protocol version: Version 4 revised (issue date: 19 May 2021).

## Background

The term “frailty” refers to a clinical condition which is characterized by an increased vulnerability to stressors and poor health outcomes resulting from a cumulative decline in multiple physiological systems, such as the musculoskeletal, endocrine, and cardiovascular system [1, 2]. While a continuous decrease in physiological capacity also occurs with normal aging, this decrease is accelerated and exacerbated in frailty [3]. Neuroscientific models of pathological aging suggest that the brain might play a major role in determining healthy or pathological aging [4, 5]. For instance, age-related gray matter reductions in the frontal [6, 7] and medial-temporal [8, 9] regions have been associated with reduced gait and memory performance, while white matter atrophy in the corpus callosum is suggested to affect bihemispheric communication [10, 11]. From a functional perspective, aging is related to reduced neural differentiation and selectivity of perceptual [12, 13] and motor [14] representations. These altered representations in turn are thought to be involved in an age-related decline in cognitive performance, such as memory [15, 16] and sensorimotor performance, including upper extremity function, gait and balance [17, 18]. In this context, an important determinant is “disuse” of the brain, characterized by a reduction of perceptual inputs, motor actions, and cognitive stimulation that are required to refine existing skills and acquire new skills [5]. When people age they tend to stereotype and simplify behaviors and the brain is likely to adapt to these less complex behaviors by simplifying the underlying neuronal representations such as cortical sensorimotor maps [4, 5]. On the neuronal level, “disuse” of the brain is thought to lead to negative changes in neuronal metabolism, such as neurotransmitter production and function [19] and neuronal architecture, including the elaboration of dendrites, spines, and synapses [20]. Therefore, the fidelity and reliability of cortical representations is thought to decline, resulting in noisy neuronal processing in sensory and motor systems, which in turn might promote maladaptive behaviors such as motor instability, coordination deficits, movement slowing, inactivity, and social isolation. Low activity levels lead to an increase in peripheral and bodily symptoms, such as a loss of muscle mass, which would increase the risk of fall and fracture [21]. Together, these interrelated factors create a self-reinforcing downward spiral of altered brain function, physical disability and age-related functional decline.

Therefore, we assume that the brain might be at the center of the vicious cycle of frailty, starting with an initial impairment and leading to an accelerated decline of physical function. As the brain is a highly plastic organ that shows adaptive as well as maladaptive plasticity [22], it might be an optimal target for innovative interventions that utilize principles of neuroplasticity to delay or even reverse cortical and behavioral age-related changes.

To date, the majority of interventional studies in older frail individuals examine physical exercise protocols including aerobic [23] and muscular strengthening exercises [24]. Physical exercise has been suggested to improve physical performance such as muscle strength, balance, and gait speed [25], but also to enhance brain health and plasticity [26]. Physical therapy in pre-frail individuals was found to increase reduced plasma levels of brain-derived neurotrophic factor (BDNF), a neuronal growth factor involved in neurogenesis and synaptogenesis [27], which suggests a key role of neuromodulatory factors in mediating the syndrome of frailty [28]. However, only few of these studies have directly evaluated the influence of physical exercise on frailty itself [29] and the optimal procedure of how to prevent or reverse the syndrome of frailty is still a matter of debate [30, 31]. Moreover, despite the evidence suggesting a close link between structural as well as functional brain changes and physical decline during aging [17, 18], interventional studies targeting the relationship between brain structure and function and frailty are surprisingly rare. In healthy adults, neuroplasticity-oriented programs, including intensive sensory, cognitive, or motor stimulation, were shown to have the potential to strengthen neuromodulatory systems, promote beneficial neuroplasticity in cortical representations, and improve neurocognitive skills that decline with aging [32–34]. As motivational and affective processes seem to be less affected by maladaptive plasticity [35], these processes provide useful means to enhance training compliance and success. With respect to the multi-system decline observed in frail individuals, computerized neuroplasticity-oriented applications using virtual environments can be more useful because they can stimulate several systems at the same time, can give immediate feedback and permit the use of everyday activities including bodily activation that are relevant for the participant’s life [36]. Therefore, we describe a randomized trial in which we use an app-based multimodal sensorimotor training in frailty.

### Objectives of the study

Our hypothesis is that intensive forms of plasticity-oriented training can improve frailty. Our goal is to enhance relevant input to the sensory and motor brain systems in order to reverse structural and functional correlates of maladaptive neuroplasticity in cortical representational maps. We aim at counteracting the “disuse” of the brain, which should lead to positive changes in neuronal metabolism and architecture and thus to an increased fidelity and reliability of cortical representations and less noisy neuronal processing. In turn, we expect these neuroplastic changes to promote cognitive, physical, and sensorimotor function, leading to an improvement in frailty status and frailty-related health indices.

Based on previous plasticity-oriented training studies in healthy subjects [32–34], our training approach will consist of a multimodal training protocol including unimodal sensory discrimination and bimodal sensory integration tasks in the visual, auditory, and tactile domain as well as a sensorimotor precision tasks (cf. [37]). The training tasks will be implemented in an app-based manner and will be embedded in a motivating virtual environment including personally relevant reinforcers to counteract the age-related reduction in motivational drive and increase adherence to and efficacy of the training. To evaluate the specificity of the sensorimotor approach, we will implement a randomized controlled trial with an app-based relaxation training serving as an active control group.

We hypothesize that the sensorimotor training will have superior effects on frailty status compared with the control training, as reflected by a pre-to-post reduction in frailty indices and an improvement in frailty-related everyday functioning. On the neuronal level, we expect a refinement of sensorimotor representation maps and an increase in neuronal efficiency in the brain. Furthermore, we expect that such neuroplastic changes will be mirrored by a pre-to-post increase in BDNF serum levels. In addition, we will compare frailty-associated outcomes between BDNF genotypes that were shown to differ in terms of both BDNF secretion and the magnitude of training-related improvement [27, 38]. In the sensorimotor domain, we expect an increase in movement speed as well as an improvement in lower extremity motor function such as balance, and upper extremity motor function such as dexterity. With regard to sensory abilities, we expect an increase in visual, tactile, and auditory performance scores. Lastly, we expect the sensorimotor training approach to enhance psychological wellbeing, as reflected by an increased perceived health status and quality of life.

## Methods

### Design

This randomized controlled trial will compare a tablet-based sensorimotor training (experimental group) and a tablet-based relaxation training (control group) in subjects suffering from frailty. Both conditions are conceptualized as a 90-day home-based intervention. Assessments will take place (1) before (baseline), (2) after 60 days (assessment 1) and (3) at the end of training (90 days; assessment 2) at the Institute of Cognitive and Clinical Neuroscience, Central Institute of Mental Health, Mannheim.

### Study population and recruitment

The expected recruitment of participants is shown in Fig. 1. Participants will be recruited from the general population as well as from geriatric hospitals via personal contact, newspaper advertisements, leaflets and online announcements. Prior to the invitation to the CIMH, potential subjects will be pre-screened for general eligibility via telephone interviews. Specific eligibility criteria will be tested and general eligibility criteria will be confirmed during the first examination appointment.

**Fig. 1 Fig1:**
[figure not shown]
Expected flow of participants and study design

The inclusion criteria will be an age of 65 to 95 years and the presence of at least one of the five frailty phenotype criteria [39], i.e. self-reported unintentional weight loss of > 5 kg in the prior year, self-reported exhaustion, low level of physical activity specified in kcal/week, muscle weakness as measured by low grip strength using a Jamar hand dynamometer, and slowness by slowed gait speed over 4.57 m. According to the phenotype model, the presence of one or two criteria is considered as pre-frailty while the presence of three or more criteria is considered as frailty [39]. We will include pre-frail as well as frail persons to investigate neuroplasticity mechanisms across a broader range of age-related functional decline, as the pre-frail stage is considered to describe a condition at high risk of progression to frailty [40, 41] and may be more amenable to change. Exclusion criteria will be: acute bone fractures within the last 3 months, immobility, paralysis or confinement to bed; stroke or neurological disorders with major cognitive or physical impairments; dementia; myocardial infarction within the last 6 months; life-time prevalence of mental disorders such as schizophrenia and other psychotic disorders, bipolar disorder, obsessive-compulsive disorder, post-traumatic stress disorder, drug or alcohol addiction; current severe major depression or other acute axis 1 mental disorders; current intake of benzodiazepines or antipsychotics; vitamin B12-, folate- or thyroid-stimulating hormone deficiency. Specific exclusion criteria will be examined during the first visit and include: cognitive impairment defined as a Mini Mental State Examination (MMSE) score of ≤ 24; severe impairments in sensory abilities (i.e. visual acuity of < 0.1; mechanical detection threshold of > 512 mN; severe or profound hearing loss according to the WHO, defined as a mean hearing threshold of > 60 dB; severe tinnitus symptomatology).

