### Randomization and blinding

Subjects will be randomly allocated on a 1:1 ratio to either the experimental or control condition. The randomization schedule will be generated electronically by a researcher not involved in the assessments. Group allocations will be kept in sequentially numbered sealed opaque envelopes. Participants will be informed about the random allocation procedure. Blinding of the investigator will not be possible because the investigator will conduct parts of the assessments and training procedures.

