With the current trial, we will employ a multidimensional characterization of frailty, including neurophysiological, physical, sensorimotor, cognitive, and functional variables, which will enable us to investigate training effects on frailty status as well as on frailty-related outcomes. Through our intervention, we will target core central nervous processing in the sensorimotor system, by which we intend to create a link between structural, functional and biological markers of neuroplasticity and potential changes in frailty status. This approach aims at identifying the underlying pathogenic mechanisms of frailty and the results may add to previous interventional studies by offering new possible explanations for training effects found in frailty status and peripheral physical outcomes, such as muscle strength and muscle mass. Moreover, our study will provide new insights into how to prevent the continuous decline and avoid adverse outcomes in the development of frailty. This is important because frailty is a condition, which evolves from a subclinical state into a state of decompensation and ultimately overt frailty in the presence of stressors [103, 104]. Depending on one’s preceding frailty state, transitions between frailty states may occur frequently over time and may also be recurrent, suggesting that frailty is a dynamic process [41]. By including frail as well as pre-frail subjects, we will be able to relate the training effects to changes in frailty status across a broad range of severity levels of pathological aging. In this context, our study might contribute to identify useful strategies, such as the maintenance of sensorimotor stimulation and function, for slowing progression in an early state and preserving older people’s physical functions, autonomy, and quality of life that future studies can be based on.

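### The sample is labelled as having frailty although pre-frail people qualify for entry: name the mixed population and adjust the primary comparison for baseline frailty

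*Protocol article*

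**What the plan says.** The label appears twice. The abstract's methods describe "applying an app-based sensorimotor home training (N = 30) in people suffering from frailty", and the Design section describes "a tablet-based relaxation training (control group) in subjects suffering from frailty". The Objectives section frames the aim in the same terms: "Our hypothesis is that intensive forms of plasticity-oriented training can improve frailty".

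The section on study population and recruitment sets a wider entry rule. A person qualifies with "the presence of at least one of the five frailty phenotype criteria", and the classification that follows is that "the presence of one or two criteria is considered as pre-frailty while the presence of three or more criteria is considered as frailty". The section states the reason openly: "We will include pre-frail as well as frail persons to investigate neuroplasticity mechanisms across a broader range of age-related functional decline". It adds that the pre-frail stage carries a high risk of progression and might be easier to change. Table 1 lists both stages as categories of frailty status. The Discussion says that, with both included, "we will be able to relate the training effects to changes in frailty status across a broad range of severity levels of pathological aging".

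The frailty phenotype is the primary outcome, measured at baseline, day 60 and day 90. The section on data analysis and handling gives a mixed repeated-measures analysis of variance over the three assessments and reads the training effect from the time-by-group interaction. On allocation, the text gives a 1:1 ratio and an electronically generated schedule, and says "Group allocations will be kept in sequentially numbered sealed opaque envelopes". It names no stratification factor and does not say that there is none.

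**The concern.** A reader of the abstract or the Design section will take the trial to be one in frail people. Under the entry rule, none of the 60 participants need be frail as the protocol defines the term. Recruitment partly or mainly from the general population, and the exclusion of immobile or bed-confined people, make a mostly pre-frail sample plausible, though the protocol gives no expected share. A positive result could then be reported as an effect in frailty while resting on few frail participants.

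The mix also bears on the primary comparison. Baseline stage is the starting value of the primary outcome, and with 30 per arm the arms can differ on it by chance. An analysis of raw change handles such a difference less well than adjustment does, and less precisely.

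**Working it through.** **1. The label against the entry rule.** The label is frailty (abstract methods, Design). Entry needs one criterion or more out of five. Frailty needs three or more, and one or two is pre-frailty. A participant with one or two criteria therefore meets the entry rule and not the label. No quota or minimum closes the gap.

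**2. The stated sample size.** Inputs from the sample size section: f = 0.25, three assessments, two groups, correlation 0.50, alpha 0.05, power 95%. For the time-by-group interaction with sphericity assumed, the noncentrality is f² × N × m / (1 − ρ) = 0.0625 × 44 × 3 / 0.50 = 16.5, with 2 and (44 − 2) × 2 = 84 degrees of freedom. Power is 0.956, and 44 is the smallest even N that reaches 0.95, so 22 per group reproduces. Dropout: 22 / 0.75 = 29.3, rounded up to 30. Nothing in this point changes these figures.

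**3. Raw change against adjustment.** Take one follow-up Y and baseline B, with equal variance σ² and correlation ρ = 0.50.
- Raw change: Var(Y − B) = 2σ²(1 − ρ) = 1.00σ².
- Adjusted for B: Var(Y given B) = σ²(1 − ρ²) = 0.75σ².
- If the arms differ at baseline by d, the expected follow-up difference without any training effect is ρd. The change contrast is then shifted by ρd − d = −0.50d. The adjusted contrast is shifted by zero.

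**4. Chance imbalance and the size of the frail stratum.** The frail share is not given; 20–50% is assumed. Simple 30:30 allocation is also assumed. With K frail among 60, the number X in one arm is hypergeometric(60, K, 30), and the arms differ by |2X − K|. The last two columns take the same share of the 44 evaluable participants and the power formula of step 2.

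| Frail share | K | P(differ by ≥ 4) | P(differ by ≥ 6) | Evaluable frail | Power in frail only, f = 0.25 |
|---|---|---|---|---|---|
| 20% | 12 | 0.33 | 0.10 | 9 | 0.30 |
| 30% | 18 | 0.40 | 0.16 | 13 | 0.44 |
| 40% | 24 | 0.43 | 0.19 | 18 | 0.59 |
| 50% | 30 | 0.44 | 0.20 | 22 | 0.70 |

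A difference of 6 among 30 per arm is 20 percentage points. These are probabilities of chance imbalance, not of bias.

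**The case against.** The strongest reply is that the mix is hidden from nobody. The recruitment section defines both stages and justifies including both, Table 1 lists both, and the Discussion repeats it. The abstract's conclusion speaks of older adults, and the phrase about suffering does not appear in the Objectives. All of that stands, and it confines the first point to labelling and the scope of conclusions.

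Several stronger readings are tempting and are not supported:
- A reader might infer that allocation is unstratified and that the comparison is therefore biased. The article is silent on stratification, which a condensed article may leave to the full protocol. Even simple randomisation gives an unbiased comparison in the mixed population.
- A reader might infer that the protocol expects the two stages to respond differently. It says only that pre-frailty may be more open to change. The moderator it names is BDNF genotype.
- A reader might take the Discussion as promising separate estimates by severity. It speaks of relating training effects to change in status within a broad sample, which is less than that.

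The likely effect of an imbalance can also be overstated. Suppose 18 of 60 are frail, split 12 and 6, and frail participants respond half as much as the pre-frail. The training arm is then 40% or 20% frail instead of 30%, and its mean training effect is 0.80 or 0.90 of the pre-frail effect instead of 0.85. That is a shift of 0.05 / 0.85, about 6%.

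Finally, it can be said that baseline is already in the analysis as the first assessment. That is true, and it prevents the baseline difference from carrying over in full. It still leaves the reversed shift and the larger variance shown in step 3 of the working.

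**Conclusion.** The label and the entry rule contradict each other, and the sample may be largely pre-frail by the protocol's own definition. How largely cannot be said, because no frail share is given. The trial can support a conclusion about a mixed pre-frail and frail population. A conclusion about frail people alone would rest on a stratum of unknown size: under the assumed 20–50% share, power there would be about 0.30 to 0.70 at f = 0.25.

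The analysis point holds in a limited form. Adjusting for baseline frailty removes the effect of chance imbalance on the comparison and, for a single follow-up, leaves 0.75 of the residual variance of raw change. This rests on the protocol's correlation of 0.50, applied to the phenotype measure, and on equal variances at both times.

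The imbalance probabilities (0.33–0.44 for a difference of 4 or more, 0.10–0.20 for 6 or more) hold only under simple 30:30 allocation and the assumed frail share. They are a reason to adjust, not evidence of a faulty allocation.

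**What to change.** - Describe the population as pre-frail and frail in the abstract's methods, the Design section and the hypotheses.
- Report how many participants per arm had one or two criteria, and how many had three or more, at baseline. Word the conclusions for that mixed population.
- In the primary comparison, take days 60 and 90 as the outcomes and enter baseline frailty (criteria count or status) as a covariate, in place of using baseline only as a response level.
- Report the training effect by baseline status with confidence intervals, marked as descriptive, because the frail stratum may be small.

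The cost is wording and one covariate. Baseline phenotype is already collected as an entry criterion, so no new data are needed. Allocation, enrolment and the 22 evaluable and 30 enrolled per group stay as they are. Stating whether allocation was stratified by frailty status would help the reader but is not needed for these changes.
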